**Figure 1 Fig1:**
[figure not shown]
**Study design and measurement time points (CONSORT chart).** AQ-10 = autism spectrum quotient short version; AAT = approach avoidance task; BDI = Beck Depression Inventory II; BSI = Brief Symptom Inventory; KIMS = Kentucky Inventory of Mindfulness Skills; MBCT = Mindfulness Based Cognitive Therapy; MCQ-30 = Metacognitions Questionnaire with 30 Items; WST = Test of Word Power; OBQ = Obsessive Beliefs Questionnaire; OCD-EP = Obsessive Compulsive Disorder Education Program; OCI-R = Obsessive-Compulsive Inventory; SBQ-R = Suicidal Behaviors Questionnaire-Revised; M.I.N.I Mini-International Neuropsychiatric Interview; INEP = Inventory of negative effects of psychotherapy; WHOQOL-BREF = World Health Organization Quality of Life-BREF; Y-BOCS = Yale Brown Obsessive Compulsive Scale.

In the proposed trial, we hypothesize that in patients with OCD who are still symptomatic (i.e., Y-BOCS >12 points) after CBT, MBCT produces a significant reduction of OC symptoms from baseline to post assessment compared to an OCD education program (OCD-EP). A cutoff-score of 12 points is an established criterion of remission proposed by Simpson et al. [11].

The long-term outcomes of MBCT and OCD-EP six and twelve months after the interventions will be compared in an explorative manner. Means, the rates of treatment responders, the rates of patients who achieved remission and the rates of patients who relapsed will be compared. Treatment response and remission will be defined according to the criteria by Jacobson and Truax [36]. Their method includes the calculation of a) a cutoff for the symptom severity after the treatment, and b) an index for a reliable symptom improvement (reliable change index, RCI). Patients who fulfill both criteria will be classified as remitted. Patients who fulfill criterion b) will be classified as responders, even if their post-treatment score is still above the cutoff. Relapse is defined as a return to pre-treatment severity as recommended by Simpson et al. [37]. Patients who were classified as remitted after the intervention will be eligible for the analysis of relapse rates [38].

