### Statistical analyses

Between-group comparisons at baseline will be performed using analyses of variance for the continuous variables and Fisher’s exact test for the categorical variables. Means and standard deviations will be calculated for descriptive purposes. The main analyses will be computed using analyses of covariance in view of statistical studies suggesting that controlling for the baseline score is superior to simple pre-post comparisons and usually leads to an increase in power. An advantage of this type of analysis over mixed models is that it accounts for baseline differences and regression to the mean (i.e. higher scores usually yield greater improvement). The rates of patients achieving response and/or remission and the relapse rates in both groups will be compared using Fisher’s exact test. The time to relapse will be estimated using Kaplan-Maier survival analyses. Survival curves will be compared using a log-rank-test. A cox-regression will be performed to analyze variables influencing the time to relapse. In order to prevent distortions, the intent-to-treat principle will be used. Multiple imputation will be adopted to estimate post-treatment and follow-up scores for non-completers (i.e. no data available at reassessment). The multiple imputation principle is considered superior to the last observation carried forward method (LOCF) [64]. When using the LOCF, follow-up data can be difficult to interpret [10].

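### Response, remission and relapse rates are given an unadjusted Fisher's exact test, which fits poorly with the planned multiple imputation and with the protocol's own case for baseline adjustment

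*Protocol article*

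**What the plan says.** Four statements in the protocol article bear on this.

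- **Test for rates** (Statistical analyses): "The rates of patients achieving response and/or remission and the relapse rates in both groups will be compared using" Fisher's exact test. No covariate, stratum or cluster term is named.
- **Missing data** (Statistical analyses): "In order to prevent distortions, the intent-to-treat principle will be used", and "Multiple imputation will be adopted to estimate post-treatment and follow-up scores for non-completers".
- **Main analysis** (Statistical analyses): "The main analyses will be computed using analyses of covariance". The reasons given are that controlling for the baseline score is better than a simple pre-post comparison, usually adds power, and deals with regression to the mean.
- **Definitions** (Study design, after the Figure 1 legend): response is a reliable change in symptom severity. Remission is that change plus a post-treatment score beyond a cutoff. Relapse is a return to pre-treatment severity and is analysed only among patients remitted after the intervention.

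The Setting section adds that centre effects are to be controlled by stratification and that treatment is delivered in eight therapy groups per arm. Study design labels the six- and twelve-month comparisons explorative.

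**The concern.** All three outcomes are functions of a severity score, which in context is the Y-BOCS. Where the score is missing it will be imputed several times, so a patient may be a responder in one imputed data set and a non-responder in another. Rubin's rules combine estimates and their variances across data sets. Fisher's test supplies neither. The article therefore pairs two methods that do not join without a further step.

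The choice also sits badly with the article's own reasoning. Response is a dichotomised pre-post change, the kind of comparison for which the article says baseline control is preferable. Yet response is tested without baseline, and without the centre by which the trial is stratified.

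At stake are the precision and readability of the responder results: a p-value with no effect size or confidence interval, from a test that gives up power. Relapse has an extra difficulty. Its denominator is the set of remitters after the intervention, and that set changes from one imputed data set to the next.

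**Working it through.** **The plan's own figure.** The Sample size section assumes d = 0.5 and power 0.8 at the 0.05 level, giving 64 per arm. The noncentral t distribution gives power 0.801 at 64 per arm and 0.795 at 63, so 128 reproduces. Adding 15% gives 128 × 1.15 = 147.2, rounded up to 148, or 74 per arm. These figures concern the continuous score; the article gives none for the rates. At 15% dropout, about 0.15 × 148 = 22 patients would have imputed status.

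**Assumptions.** The article states no response rates, intracluster correlations (ICC) or remitter numbers. Those used below are assumptions, and two-sided testing at 0.05 is assumed throughout.

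**1. Conservatism on independent data.** Every 2×2 table is enumerated. Size or power is the sum, over tables with p ≤ 0.05, of Bin(x; n, p1) × Bin(y; n, p2). The comparator is the uncorrected chi-square (pooled z) test.

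| n per arm | Quantity | Fisher | Chi-square |
|---|---|---|---|
| 64 | size, common rate 20% | 0.030 | 0.048 |
| 64 | size, common rate 30% | 0.031 | 0.051 |
| 64 | size, range over 10%–50% | 0.023–0.035 | 0.045–0.054 |
| 64 | power, 20% v 40% | 0.630 | 0.707 |
| 64 | power, 30% v 50% | 0.587 | 0.654 |
| 74 | power, 20% v 40% | 0.705 | 0.769 |
| 20 (assumed remitters) | power, relapse 20% v 40% | 0.192 | 0.291 |

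For 20% v 40% the loss is 0.707 − 0.630 = 0.077 at 64 per arm and 0.769 − 0.705 = 0.064 at 74.

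**2. Can the results be combined after imputation?** A simulation used 74 per arm, 15% missing, 20 imputations, pre-post correlation 0.5, and a true d of 0 or 0.5.

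| Route | Rejection under null | Power at d = 0.5 |
|---|---|---|
| Risk difference, Rubin's rules | 0.039 | 0.55 |
| Log odds ratio, Rubin's rules | 0.031 | 0.52 |
| Median Fisher p-value | 0.036 | 0.53 |

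All three routes work and perform alike. Pooling an unadjusted estimate therefore adds an effect size and interval, but no real power over the median p-value.

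**3. Baseline adjustment.** A further simulation with assumed d = 0.5 and pre-post correlation 0.5 gave power of about 0.50 for Fisher's test, 0.58 for unadjusted logistic regression and 0.63 for logistic regression adjusted for baseline. The levels depend on where the response threshold falls; the ordering is what matters.

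**4. Therapy-group clustering.** With eight groups of eight per arm, the design effect is 1 + (8 − 1) × ICC, which is 1.35 at ICC 0.05 and 1.70 at ICC 0.10. Beta-binomial simulation of Fisher's test at common rates of 20% and 30% gave these true sizes:

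| ICC | True size |
|---|---|
| 0 | 0.029–0.031 |
| 0.01 | 0.036–0.037 |
| 0.05 | 0.061–0.063 |
| 0.10 | 0.095–0.099 |

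The conservatism in step 1 therefore holds only if clustering is negligible.

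**The case against.** **Pooling is possible.** A reader might infer that the rates cannot be pooled, so that the analyst must test one filled-in data set or fall back on completers, and that no valid result can be produced. The documents do not support this. The article prescribes neither of those courses, and step 2 shows that effect estimates, or the Fisher p-values themselves, can be combined with acceptable error rates. What stands is narrower: the named test cannot go directly into Rubin's rules.

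**A combining rule may be left to a fuller document.** This is correct, and its absence from a journal article is no finding. That Fisher's test is run on imputed status is also an inference, though a natural one, since otherwise these outcomes would fall outside the stated intent-to-treat rule. The point rests on the two methods that the article does fix.

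**The log-rank test.** It is tempting to extend the criticism to it. That fails: the test has an observed-minus-expected numerator with a variance, which gives an approximate log hazard ratio and standard error. A Cox regression is planned as well.

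**Importance.** A reader might treat the rates as the main long-term comparison. The article calls the long-term comparisons explorative and lists means beside the rates.

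**Conservatism is not an error.** On independent data Fisher's test keeps its level, and the loss is one of power. The chi-square comparator slightly exceeds 0.05 at some rates (up to 0.054 at 64 per arm), so part of its advantage there is not free. Response also uses the baseline score already, through the change. These points stand and keep the matter minor, but adjusting for baseline still gained power in step 3.

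**Conclusion.** The concern holds in limited form. For outcomes derived from multiply imputed scores, the article fixes an unadjusted test that gives no poolable estimate and sets aside both its own argument for baseline control and the centre stratification. On independent data the cost is a true size of about 0.03 and roughly 6 to 8 points of power at assumed rates of 20% v 40%. Baseline adjustment adds about 5 points more over unadjusted logistic regression (0.63 − 0.58) in the assumed scenario. With therapy-group clustering at an ICC of 0.05 or more, the error rate would exceed 0.05 instead, so the net direction is unknown. Nothing here touches the primary analysis of covariance, and the affected comparisons are secondary or explorative. It is a worthwhile improvement, not a flaw that invalidates results.

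**What to change.** **Response and remission.** Derive both within each imputed data set. Fit a logistic model with arm, baseline Y-BOCS and centre, allowing for therapy group by a random effect or robust variance. Pool by Rubin's rules and report the odds ratio or risk difference with its confidence interval at each assessment after treatment. Keep Fisher's test as a complete-case check.

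**Relapse.** Rely on the Cox regression already planned, pooled across imputations. Make explicit that it contains treatment arm, because the article describes it only as examining variables that influence time to relapse. State how the remitter denominator is handled when it differs between imputed data sets.

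**Cost.** A change of analysis wording and slightly more programming. The model-based test is not exact when cells are small, which matters most for relapse. No change to data collection or sample size is needed.

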## Discussion

To the best of our knowledge, this is the first study to evaluate the efficacy of MBCT in patients with OCD as a complement to CBT with ERP. Based on the results of the pilot study outlined above, the proposed project aims at systematically examining the impact of MBCT as a new treatment option for patients with OCD who do not sufficiently benefit from CBT with ERP, who suffer a relapse or who experience difficulties in partaking in this kind of treatment.

We also intend to undertake a wide range of additional analyses. Various factors have been discussed that could, individually or in their combination, mediate positive effects of mindfulness training in patients with OCD. One of them is an increased willingness to experience difficult thoughts, feelings and body sensations [32]. A study on patients with Social Phobia provided evidence that Mindfulness Based Stress Reduction, a therapy program that is closely linked to MBCT, improves emotion regulation skills in patients with social phobia [65]. This could be especially relevant for patients with OCD, because emotion regulation has been identified as a common function of OC symptoms [66]. We therefore will examine changes of distress tolerance and their association with therapeutic outcome. Moreover, the mindfulness approach might be helpful to question metacognitive styles and beliefs that maintain OCD such as thought-action fusion (TAF) [67,68] and thought control [69]. Thus, we will use measures of dysfunctional metacognitions and believes in explanatory analysis in order to identify factors that mediate or moderate therapeutic effects. Besides, we will evaluate the impact of self-compassion on changes of symptom severity. Self-compassion has shown to be below average in OCD patients [70] and was a better predictor of symptom severity and quality of life than mindfulness in patients with depression and anxiety disorder [71]. Especially for patients with OCD, self-compassion could be helpful to disengage from struggling with shaming obsessions such as violent or sexual intrusions and to deal with them in an accepting, not self-judging manner. Furthermore, subgroup analyses on the influence of baseline characteristics, such as baseline severity, sociodemographic variables, comorbid mental disorders and treatment motivation are planned.

We will further examine approach avoidance tendencies as measured by the AAT, because patients struggle to change their obsessions and compulsions even though they have insight into the irrationality of their fears. According to 2-systems models, (e.g. [72]) behavior is influenced by an automatic, inflexible impulsive system and a slower and more flexible reflective system. In OCD it is assumed that in the impulsive system, strong connections between obsessive related concepts and items are associated with danger [73]. Therefore the AAT offers us a chance to detect changes in behavioral tendencies that patients may not be able to report.

There is a growing body of empirical evidence showing that mindfulness-based interventions are effective in increasing positive and/or in decreasing negative affect in a variety of clinical conditions [74–77]. Since there is no study exploring changes in positive and negative affect caused by MBCT in OCD patients so far, we decided to use the ESM paradigm in order to fill this gap and to provide further insight into the nature of OC symptoms and associations with affective states as they occur in the natural environments of participants.

Regarding recruitment of participants, we decided to not exclude patients who currently undergo psychopharmacological or psychotherapeutic treatment. One reason for the liberal acceptance of concomitant treatments refers to practical considerations. We assume to reduce the non-eligibility rate and to improve external validity, since the vast majority of patients with clinically relevant OCD receive some kind of treatment. Another reason is the chance to conduct subgroup analyses in order to evaluate the efficacy of MBCT in patients with OCD as a complement to current treatment. However, the acceptance of concomitant treatment may also constitute a limitation of the study, since the power to detect a difference between MBCT and OCD-EP might be reduced due to effects of other treatment modalities.

Finally, we hope that the 6-month and the 12-month follow-up data will provide important insights in longterm-effects of mindfulness-based interventions in OCD on severity of symptoms and related measures such as obsessional beliefs or quality of life.

In view of the large percentage of OCD patients who do not sufficiently benefit from conventional CBT with stimulus exposure and response prevention, there is a strong urge to find additional or complementary treatment options. The present study wants to shed light on the role of MBCT as a valuable intervention to boost the gains from cognitive-behavioral approaches in OCD by opening up new avenues of relating to OC symptoms.
